## Abstract

**Background:**

Although mild to moderate mental health problems are common and often debilitating, treatment options in primary care settings in New Zealand are often severely limited for patients with these conditions. Previously, we developed an ultra-brief intervention (UBI) to address mild to moderate psychological concerns, designed to be delivered by primary care clinicians. Recent feasibility testing, including an adaptation for Māori individuals (the indigenous people of New Zealand), showed that the brief intervention was feasible and acceptable to both clinicians and their patients. This protocol describes a large pragmatic randomized controlled trial of our UBI in primary care settings across the greater Wellington region, compared with practice as usual.

**Methods/Design:**

We are using a two-arm cluster randomized controlled trial, with primary care practices randomized to exclusively deliver either the UBI or practice as usual to all their recruited participants. The structured, guided self-help UBI is delivered in three brief general practitioner (GP) appointments over a five week period. Participants are invited into the study based on partner primary health organization access criteria (youth, people with low income, or people with Māori or Pacific Island heritage). Improvements in mental health from baseline to post-treatment will be compared between the intervention and control groups using a mixed-models application of analysis of covariance. Data analysis will be on an intention-to-treat basis, to increase the real-world relevance of UBI and to meet the study's objective of releasing UBI to primary care clinicians nationwide.

**Discussion:**

The UBI is a first-line intervention tool for GPs that models the stepped care approach advocated in New Zealand, against a background of limited access to treatments for often-overlooked patient groups. It is proposed to be accessible to clinicians and patients alike, with the potential to be relevant to primary care clinicians across New Zealand.

**Trial registration:**

Australian New Zealand Clinical Trials Registry ACTRN12613000041752.

## Background

The recently released Global Burden of Disease Study (GBD 2010) highlighted mental health and substance use as leading causes of disability and a worldwide health priority [1]. Mental and substance use disorders now represent 7.4 % of disability-adjusted life years [2] and 6 of the 20 leading causes of disability are attributable to mental health issues [3]. In line with international findings, just under 40 % of the New Zealand population had met criteria for a diagnosable mental disorder during their life, and roughly a fifth had experienced a mental disorder in the previous year [4].

In New Zealand, as in other OECD countries, mental health problems are very common in primary care and general practice. It is estimated in New Zealand that 50–70 % of mental health concerns are managed exclusively at the primary care level [5]. Primary mental health care is thus appropriately concerned with the promotion of mental health, and the prevention, assessment, early intervention, treatment and ongoing management of mental health concerns [5].

Primary care services in New Zealand are expected to respond to more of the mental health needs of the population, as secondary services become more targeted towards severe and enduring mental illness. However, treatment options for mental health problems at the primary care level are limited [5]. Between 26.5 % and 29.8 % (men and women, respectively), of primary care patients in New Zealand are thought to have mild to moderate mental health concerns by their GPs [6]. People with these problems can experience significant impairment in functioning and suffering [7, 8], indicative that treatment is required [9]. Individuals with ‘minor’ or mild to moderate depressive symptoms can have similar levels of functional impairment and place similar demands on mental and physical health services as those with more recognized diagnoses, such as major depression [10]. Some individuals with mild to moderate mental health issues will go on to develop severe depression [11, 12].

Unsurprisingly, there is a large unmet need for treatment options for common mental health concerns in primary care services in New Zealand [5, 13]. Although GPs identified that 90 % of patients who received an explicit diagnosis received treatment for mental health needs, as few as 22 % of people with mild to moderate mental health symptoms received any form of formal help [14].

It is important that primary care provides services to those who are disadvantaged in terms of access to mental health care. This includes those at socioeconomic disadvantage and many of those from Māori (the indigenous people of New Zealand) and Pacific Island populations [4]. Rates of common mental disorders in general practice settings are higher for Māori than non-Māori, although Māori are less likely than non-Māori to have been identified by their GP as having mild to moderate symptoms (15.3 % versus 23.2 %) [15].

Primary care practitioners need a range of interventions to call on, and evidence is emerging for ‘ultra-brief’ and self-help interventions, such as bibliotherapy, for mild to moderate syndromes [16–18]. It is critical that interventions are developed that are suitable for delivery by clinicians in primary care settings without the need for referral to other professionals, such as counsellors. This aids accessibility in that many people may feel more comfortable discussing concerns with a trusted GP than with a ‘counsellor’. Furthermore, referral to external services may not be possible, owing to waiting lists, criteria for service entry, or due to a lack of funds. It is also important that such interventions can be accommodated within the usual time frames of general practice consultations. A standard individual consultation in many OECD countries would last between 10 and 15 minutes, though consultation for any mental health problem might be spread over three or four visits.

In keeping with this unmet need for treatment, we developed and feasibility-tested an ultra-brief intervention (UBI) for mild to moderate mental health problems in New Zealand primary care [19]. The UBI uses a guided self-help format, involving three brief, structured face-to-face sessions with a GP, supported by self-help booklets across four topics: stress management, relationships, harmful behaviors, and bodily stress. These topics were selected because 36 % of general practice attendees report anxiety, depression or substance use, or a combination of these issues [6]. In addition, symptoms of bodily stress (previously referred to as medically unexplained symptoms) are common presentations in primary care settings [20, 21], and are being considered as a new diagnosis (ICD-11-PHC) in the forthcoming International Classification of Diseases [22]. This was reflected in GP feedback that indicated a need for resources on bodily stress. The face-to-face intervention and booklets were adapted for Māori providers and patients, and were found to be relevant and acceptable to both clinicians and their Māori patients [23, 24].

The UBI fits with a stepped care approach to mental health care in New Zealand, in which interventions range from self-help to professional help-seeking, depending on symptom severity and response to treatment. The UBI requires minimal training, no specialist counselling knowledge and incorporates techniques already familiar to most primary care clinicians. It requires only one hour of face-to-face time with the patient in total. Furthermore, it can feasibly be delivered in primary care without referral to another professional, therefore improving accessibility and acceptability of treatment for patients. In a recent feasibility test of the UBI, high levels of acceptability among primary care clinicians and patients were found, and the UBI yielded significant clinical improvements at 3 month follow-up, for both non-Māori [19] and Māori [23].

Despite evidence for the individual elements within the UBI, there has been no randomized controlled trial of the effectiveness of such a therapy delivered routinely in primary care. Thus, the aim of this trial is to investigate the clinical effectiveness of UBI for individuals who present with mild to moderate mental health needs in primary care settings compared with practice as usual, in a randomized controlled trial in a real-world study design. Specifically, we have the following objectives:To compare mental health state (as measured by K10 scores) at 26 weeks between the UBI and practice-as-usual study arms. This is the primary outcome measure.To compare levels of distress (depression and anxiety) and functioning (work, social and relationship) at 8 and 12 weeks between the UBI and practice-as-usual study arms. These are the secondary outcome measures.

## Methods/Design

We are using a pragmatic two-arm single-blinded, cluster randomized controlled trial of the UBI for mild to moderate mental health concerns compared with practice as usual, in a primary care setting. General practitioners have been randomized by practice to exclusively deliver either the UBI or practice as usual to all their recruited participants. The GPs are treated as the clusters in the study design (while there will be clustering by GP practice, the GPs are being treated as the unit of analysis, as practitioner attribute is anticipated to be a higher source of variability in outcomes.)

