### Recruitment methodology and randomization

Initial recruitment of GP practices was with the support of the partner primary health organization. The GPs were identified using primary health organization and practice lists. All of the GP practices contracted under the partner primary health organization were contacted (*N* = 52) and invited to participate in the study, and an effort was made to contact all of the GPs within these practices by email, telephone or in person. A total of 21 practices consented to participate in the study. To safeguard against gross imbalances in number of GPs per study arm, a cluster randomization schedule was created, with randomization restricted by the numbers of GPs in each practice (two medium-size practices were combined in one stratum to balance one very large practice). Of the 63 GPs who originally consented to participate, 59 completed a single two-hour training session (previously described [19]) and returned a signed consent form. Practices agreeing to take part were randomly assigned to provide either the brief intervention or practice as usual to eligible patients attending their surgeries. To ensure approximately equal numbers of GPs per study arm, randomization of practices was conducted within five blocks, according to the number of participating GPs: one, two, three, four, or more than four GPs. An additional two practices dedicated to youth health that are not part of the partner primary health organization were included and randomized into each arm of the study (i.e., these two practices formed their own stratum). Practices assigned to the practice-as-usual study arm will receive training in the intervention at the end of the study.

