### Statistical methods

#### Sample size and power analysis

Sample size was calculated using a simulation approach, based on standard deviations from a sample of similarly eligible patients from the UBI development study (standard deviation of post-treatment scores = 7.5; unpublished data). For 80 % power to detect a difference in K10 improvement scores of 6 points in the UBI arm, compared with 2 points in the control arm, would require 15 GPs per arm, each recruiting eight completing patients on average (*n* = 240 total with complete data). Adjusting for loss to follow-up of 20 % gives a recruitment target of ten patients per GP. The simulation settings roughly correspond to an intraclass correlation of 0.15 for considering the clustering of patient scores due to GPs: this corresponds to the intraclass correlation from the unpublished data from the development study. A power analysis for the secondary HADS scale outcome indicated that the study would have 80 % power to detect a difference of 3.2 points between groups (based on a standard deviation for the total score of approximately 6 for a general practice sample [31], with the same sampling design, and assuming a similar intraclass correlation for the HADS scale as used for the K10 measure (empirical data not available)).

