#### Analysis

The statistician performing data analysis will be blinded to the intervention or control status of participants (both practices and patients). For the primary outcome, K10 scores at 26 weeks will be compared between the intervention and control groups using a mixed linear models application of analysis of covariance (comparing post-intervention scores between groups, adjusting for intake score as a covariate, and treating GP clusters as random effects). Data analysis will be conducted on an intention-to-treat basis. Missing data for the 26-week follow-ups will be handled through the mixed linear models approach to the data, which allows for participants with missing data for the final follow-up to be included in analyses (this in effect estimates a final outcome value conditional on the observed data at other follow-up times.) This missing data method is valid under the assumption that the missing observations are missing at random, conditional on the observed data [32, 33]. The null hypothesis for this test is that the K10 scores at 26 weeks (adjusted for baseline score) are not different in the intervention and control groups.

To account for stratification by type of practice (youth-health focused practices, in contrast to unrestricted GP practices) we will conduct a sensitivity analysis looking at data just from the unrestricted GP practices (i.e. excluding the two practices in the youth-health stratum).

For the secondary analysis, differences in mean scores on the K10 outcome will also be reported at 8 and 12 weeks (using the same methods as before, within the mixed linear models framework). Analysis of the HADS combined score will utilize the same methods as for the K10 outcome.

The findings of this study will be reported in line with the CONSORT statement, as adapted for cluster randomized trials [34].

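### Practices are randomised, but the primary K10 model has only a GP random effect, so correlation between GPs of the same practice is left out and the standard error is too small

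*Protocol article*

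**What the plan says.** The unit of allocation is the practice. The Methods/Design section says "General practitioners have been randomized by practice to exclusively deliver either the UBI or practice as usual to all their recruited participants", and the section on recruitment methodology and randomization says "Practices agreeing to take part were randomly assigned to provide either the brief intervention or practice as usual".

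The unit of analysis is the GP. Methods/Design concedes the practice level and then sets it aside: "while there will be clustering by GP practice, the GPs are being treated as the unit of analysis", the reason being "as practitioner attribute is anticipated to be a higher source of variability in outcomes". The Analysis section follows this through. The primary comparison of K10 at 26 weeks is a mixed-model analysis of covariance, "adjusting for intake score as a covariate, and treating GP clusters as random effects".

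The sample size section likewise uses a single intraclass correlation (ICC), 0.15, attributed to GPs. The article names no practice random effect, no practice-robust standard error and no practice-level sensitivity analysis. Its one sensitivity analysis drops the two youth practices.

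**The concern.** The GP random effect deals with correlation among patients of the same GP. It does not deal with correlation between patients of different GPs in the same practice. Those GPs share one allocation, so a practice effect does not average out between the arms within a practice and goes in full into the treatment contrast. This is true however the practice variance compares with the GP variance, so the stated reason does not support the choice.

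The consequence is a model standard error that is too small, a confidence interval that is too narrow, and a test of the primary null hypothesis that rejects too often. The model also treats about 59 GPs as separately allocated (59 − 2 = 57 degrees of freedom), while 23 practices were allocated (23 − 2 = 21). The Analysis section applies the same methods to K10 at 8 and 12 weeks and to HADS, so those results are affected too. The trial is meant to support national release of the intervention, so an anti-conservative primary test matters.

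**Working it through.** **Inputs from the protocol.** SD 7.5 ("standard deviation of post-treatment scores = 7.5; unpublished data"); difference 6 − 2 = 4 K10 points at 80% power; 15 GPs per arm with 8 completers each; GP-level ICC 0.15; 21 practices plus 2 youth practices; 63 GPs consented and 59 trained; randomisation blocks running from one to more than four GPs per practice.

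**Inputs assumed.** Two-sided 5% level (none is stated). Same-GP ICC held at 0.15, of which a part ρ is shared across the practice. The protocol gives no value for ρ, so 0.02, 0.05 and 0.075 are used. The last is half of 0.15, the most that is compatible with the GP share being the larger. The number of GPs in each practice is also assumed.

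**1. The plan's own figure.** Design effect = 1 + (8 − 1) × 0.15 = 2.05. Without clustering, 56 patients per arm are needed. 56 × 2.05 = 114.8 per arm, and 114.8 / 8 = 14.35, rounded up to 15 GPs per arm, or 240 patients. The planned standard error is 7.5 × √(2 × 2.05 / 120) = 1.39. Power is 79.5% by noncentral t on 28 df. The stated 240 therefore reproduces, but only with GPs as independent clusters.

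**2. GPs per randomised unit.** 59 / 23 = 2.6. If the GP counts exclude the youth practices, up to 63 / 21 = 3.0.

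**3. With the practice level included.** For m patients per GP and g GPs per practice, design effect = 1 + (m − 1) × 0.15 + (g − 1) × m × ρ. With m = 8 and g = 3 (5 practices of 3 GPs per arm) this is 2.05 + 16ρ:

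| ρ | Design effect | True SE | Ratio to 1.39 | GPs per arm for 80% power (56 × design effect / 8) |
|---|---|---|---|---|
| 0.02 | 2.37 | 1.49 | +8% | 17 |
| 0.05 | 2.85 | 1.63 | +18% | 20 |
| 0.075 | 3.25 | 1.75 | +26% | 23 |

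**4. Type I error of the GP-only analysis, by simulation under the null.** Fitting the same 240 completers to the 59 GPs trained gives 240 / 59, about 4 per GP; 8 per GP is the planned figure.

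| Layout | ρ = 0 | 0.02 | 0.05 | 0.075 |
|---|---|---|---|---|
| 59 GPs in 23 practices, about 4 completers per GP (REML, 4,000 trials) | 5.0% | 6.2% | 8.8% | 10.9% |
| Same, about 8 completers per GP | 4.9% | 7.2% | 9.9% | 13.9% |
| 5 practices of 3 GPs per arm, 8 completers (GP-level test, 20,000 trials) | 4.9% | 6.8% | 9.8% | 12.0% |
| 29 GPs in 11 unequal practices per arm, 8 completers (GP-level test, 20,000 trials) | 5.2% | 7.1% | 11.1% | 13.8% |
| 15 single-GP practices per arm, 8 completers (GP-level test, 20,000 trials) | 5.1% | 4.8% | 5.0% | 5.1% |

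In the first layout at ρ = 0.05 the model SE is 1.21 against a true SE of 1.41. In the third layout the model SE stays at 1.36 to 1.38 while the true SE rises from 1.48 to 1.73 over ρ = 0.02 to 0.075. The ρ = 0 column and the single-GP row serve as checks: the error is about 5% exactly where theory says it should be.

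**5. Power of a valid test.** With 5 practices of 3 GPs per arm, a practice-level test at the planned 240 has about 65%, 57% and 52% power at the three values of ρ. With 29 GPs in 11 practices per arm and 8 completers each (464 patients), it has 87%, 85% and 82%.

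**The case against.** Several points on the other side are fair.

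- The GP effect does capture same-GP correlation, which the protocol expects to be the larger part. For practices with one participating GP, nothing is lost. What is left out is only the correlation between GPs within a practice.
- The size of the error depends on a practice ICC that the protocol does not give. At 0.02 with four completers per GP, the type I error is only a little above 6%. The figure near 11% needs practice and GP variance to be equal, the edge of what the protocol believes.
- The simulations leave out baseline K10 and the earlier follow-ups, which the planned model uses. Adjustment may shrink both variance components. The spread of GPs over practices is assumed.
- The contrast of 57 with 21 degrees of freedom is sharper than a nested model would give. Satterthwaite or Kenward-Roger values depend on the estimated variances and can lie between. With about 23 practices the practice variance is often estimated as zero: in 42% of simulated trials at ρ = 0.02 with four completers per GP. Fixing 21 degrees of freedom was then conservative (3.5% rejection at ρ = 0).

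These points limit how exactly the inflation can be stated. They do not restore the reason given for dropping the practice level. The protocol itself expects practice clustering and enrols practices with several GPs, and those are the two conditions for the standard error to be too small. Nor is this a detail left to a separate analysis plan: the GP-only choice is stated and defended in the article.

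**Conclusion.** The concern holds. The protocol fixes an analysis that omits variation at the level of randomisation, for a reason that does not bear on the matter. The direction of the error is certain, given any practice variance above zero and more than one GP in some practices. Its size is uncertain. For a practice ICC of 0.02 to 0.075 within a same-GP ICC of 0.15, the nominal 5% test has a type I error of about 6% to 11% with four completers per GP, and about 7% to 14% with eight. These figures assume the layouts shown and no baseline covariate. The planned power is overstated for the same reason: it is 80% only if GPs are independent. This should be corrected before the primary analysis is run.

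**What to change.** Fit random intercepts for practice and for GP nested within practice in the primary model and in every secondary model (K10 at 8 and 12 weeks, HADS). Use Kenward-Roger or Satterthwaite degrees of freedom, and keep the practice term whatever its estimated variance. Replace the parenthetical statement in Methods/Design with wording such as: *practice is the unit of randomisation; the analysis accounts for practice and for GP within practice*. Amend the Analysis section to match.

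Recheck power at practice level over a stated range of practice ICC, using the actual number of GPs per practice.

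The cost is small. Practice membership is known from the randomisation, so no new data are needed. The confidence interval becomes wider, and power at 240 completers is lower than stated if only 15 GPs per arm contribute. Having 59 trained GPs may offset this, depending on how many patients each recruits.

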### Setting

The study is being conducted in general practices in the greater Wellington region, New Zealand.

### Participants

This is a real-world trial supported in the framework of existing treatment services. Patients aged between 18 and 65 who are identified by their GPs in a routine appointment as experiencing distress and needing a mental health intervention are eligible to participate. All participants must also score 35 or less on the Kessler 10 (K10) assessment scale, which measures global psychological distress, during their initial GP consultation. These scores were selected to indicate mild to moderate levels of psychological distress. There is no lower cut off score, since initial inclusion is based on the GP identifying a clinical problem that would be managed at the GP level. Previous work in New Zealand general practice using the K10 has demonstrated that clinicians do not select patients with very low K10 scores (<20) for clinical intervention [5]. The K10 demonstrated sensitivity and specificity for anxiety and depressive disorders, where scores exceeding 30 indicate a ‘very high’ risk of having a mental disorder [25]. This study follows previous study protocols [19, 23], where scores falling between 30 and 35 on the K10 were indicative of mild to moderate levels of psychological distress rather than a diagnosis of major psychiatric disorder, and were therefore included. Individuals receiving treatment with anti-depressant or other psychiatric medications are eligible to participate in the study.

Exclusion criteria for patients are non-fluency in English (as the intervention is an English-language based ‘talking therapy’), significant levels of cognitive impairment, as determined by the GP, and recent or acute suicidal ideation (i.e., within the previous 2 weeks). Chronic low level suicidality being managed by the GP does not exclude an individual from participating, except for those individuals who have high current levels of distress, indicated by K10 scores exceeding 35 at baseline. General practitioners are informed of patients who have high scores or suicidality at screening, or for whom referral to appropriate secondary mental health services is indicated, and these patients would not be eligible to participate further in the study. Participants are still eligible to participate if their K10 scores increase above 35 during the study, and if, in the active intervention group, they have also completed two out of three sessions of the UBI.

Inclusion criteria are based on the access criteria of a local partner primary health organization to psychological therapies. The criteria for access are specifically targeted at youth (defined as 18 to 24 years old), and, for individuals aged 25 years or older, patients with low income, or Māori or Pacific Island heritage. In line with the focus on access for youth to mental health interventions, two youth-specific services were also included in the study. The GP practices were eligible for inclusion in the study if they were members of the local partner primary health organization: no further inclusion or exclusion criteria were applied at the practice level.

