### Intervention

The UBI is a structured and guided self-management program, and can be delivered by a GP after a single two-hour training session. Participants who have consented and completed the intake data collection (K10 and baseline measurements) will receive the GP-led intervention in three short, structured face-to-face sessions (one 30 minute and two 15 minute sessions) over a five to six week period. The UBI is a self-help approach based on structured problem solving and cognitive behavior therapy and is supported by self-help booklets on relationships, bodily stress, breaking habits and stress management. Booklets are provided to the patient after the first session, to be used in the following session. The intervention resources have been adapted to better meet the needs of Māori participants, and include Māori imagery, Te Reo (language), wairua (spirituality), whanau (family) and whakatauki (proverbs), the face-to-face sessions can include whakawhanaungatanga (the process of forming connections), and offer karakia (prayer) at the start. Measures will be collected by the research assistant before (baseline) and after treatment (8, 12, and 26 weeks). Participants can revert to practice as usual following the completion of the brief intervention. Participants can commence mental health medications at any time, or withdraw from the study and change to another intervention pathway during UBI, if deemed clinically necessary by their GP or other healthcare providers. Participants are considered to have completed the intervention if they attended at least two out of the three sessions with their GP. Increasing K10 scores during the study are not a reason for withdrawal for either intervention or control group.

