### Practice as usual

Participants in the practice-as-usual study arm will receive GP support delivered according to their practice (and available existing services) as usual. Practice as usual typically consists of supportive counselling in a 15 minute face-to-face consultation, the provision of psychotropic medication, referral to psychological or other counselling options, or referral to relevant community services. All measures will be collected according to the same timescale and methodology as the intervention arm. The UBI is excluded as a component of practice-as-usual arm.

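### The condition for staying in the trial after K10 rises above 35 applies to the UBI arm only and conflicts with the no-withdrawal rule and with intention-to-treat; the two rules need reconciling

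*Protocol article*

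**What the plan says.** Four parts of the protocol article bear on who stays in the trial.

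- **Participants.** At entry, "All participants must also score 35 or less on the Kessler 10 (K10) assessment scale". A later rise above 35 does not end eligibility, but in the UBI arm this holds only "if, in the active intervention group, they have also completed two out of three sessions of the UBI". No condition is set for the control arm.
- **Intervention.** "Increasing K10 scores during the study are not a reason for withdrawal for either intervention or control group". The same section sets the completer definition at the same threshold: "Participants are considered to have completed the intervention if they attended at least two out of the three sessions with their GP". It also says that participants can start medication, or can "withdraw from the study and change to another intervention pathway during UBI, if deemed clinically necessary by their GP or other healthcare providers".
- **Practice as usual.** The comparator already includes "the provision of psychotropic medication, referral to psychological or other counselling options, or referral to relevant community services". No withdrawal is attached to any of these. Measures follow the same timing and method as in the UBI arm.
- **Analysis.** "Data analysis will be conducted on an intention-to-treat basis"; the Abstract says the same. Missing 26-week scores are handled by the mixed model, assuming they are missing at random given the observed data.

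**The concern.** The two statements on rising K10 cannot both be followed. The session condition cannot be read as entry screening, because it applies during the study and counts sessions attended after randomisation.

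The condition combines the primary outcome scale with adherence, and it acts in one arm. If a patient who fails it leaves follow-up or the analysis, the UBI arm loses people who both worsened and did not complete, while matching control patients remain. That departs from intention-to-treat, and recruiting more patients does not remove the resulting shift.

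The sentence on changing pathway during UBI could add to one-sided loss if it is taken to end follow-up. In the control arm, referral elsewhere is simply part of the comparator.

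**Working it through.** **1. The rules side by side**, for a patient whose K10 rises above 35 with fewer than two sessions attended:

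| Rule | UBI arm | Control arm |
|---|---|---|
| Participants section | no longer eligible, by implication | stays (no session condition) |
| Intervention section | stays | stays |
| Analysis section (intention-to-treat) | analysed as allocated | analysed as allocated |

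The conflict is confined to the UBI cell of the first row.

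**2. The plan's own sample size reproduces.** Inputs from Sample size and power analysis: difference 6 − 2 = 4 points, SD 7.5, intraclass correlation 0.15, 8 completers per GP, 80% power. Two-sided 5% is assumed, since no level is stated.

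- Per arm without clustering: 56.
- Design effect: 1 + (8 − 1) × 0.15 = 2.05.
- 56 × 2.05 = 114.8 per arm; 114.8 / 8 = 14.35, so 15 GPs per arm and 2 × 15 × 8 = 240 completers, as stated.
- Power at 120 per arm: 79.5% (t test, 28 df) or 82.3% (normal approximation).
- Recruitment: 8 / (1 − 0.20) = 10 per GP, as stated.

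The sample size is not affected by this point.

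**3. Shift if the condition removes patients.** A large-sample simulation with no true effect dropped UBI patients who had a post-baseline K10 above 35 and fewer than two sessions. It then ran analysis of covariance on baseline K10. These inputs are assumptions, not in the document: baseline mean 26 to 31, baseline SD 5, correlation between scores 0.4 to 0.6, a mean fall of 2 points in both arms, and 25% to 100% of patients above 35 having fewer than two sessions.

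- Everyone kept as allocated: difference 0.0.
- Condition applied: −0.07 to −0.69 points, toward UBI in all 18 scenarios, with about 2% to 20% of the UBI arm removed.
- Against the target: 0.07 / 4 = 2%; 0.69 / 4 = 17%.
- Planning standard error: 7.5 × √(2 × 2.05 / 120) = 1.386. At the largest shift, 0.69 / 1.386 = 0.50, so the two-sided 5% false-positive risk becomes about 7.9%.

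The range depends on how closely the triggering score tracks the 26-week score. With a residual correlation of 0.6 between the 8-week and 26-week scores, complete-case shifts reached about 1.0 point. The 0.7 figure is therefore not a ceiling.

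**4. Does the planned mixed model recover it?** Outcomes are collected at 8, 12 and 26 weeks, and the UBI course takes five to six weeks, so no research K10 is scheduled during the sessions.

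- If the 8-week score is the trigger and stays in the model, likelihood estimation gave −0.03 to +0.03, essentially zero. This assumes that attendance does not itself predict outcome.
- If removal happens during the course, no post-baseline score is scheduled before it. A patient with only a baseline score adds nothing when baseline is a covariate.

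The document does not say which score triggers the condition.

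**The case against.** The strongest reply is that the bias depends on one reading of one sentence. The Participants section speaks of eligibility to participate. It does not say that questionnaires stop or that data are deleted. The Intervention section rejects withdrawal for rising K10, both arms are measured on the same schedule, and the analysis is by intention-to-treat. If those statements govern, nobody is lost. This stands: the bias is conditional. It does not remove the conflict, because staff who apply the Participants section as written would act differently in the two arms.

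A reader might also infer that UBI patients who change pathway are removed, in contradiction of the Intervention section. The document does not support that. The sentence "withdraw from the study and change to another intervention pathway during UBI" is itself in the Intervention section and is permissive: it states what participants can do. Nothing denies control patients the same freedom. At most, the wording could add to one-sided loss if it is read as ending follow-up and if those who change are doing worse. No rate is given, so that part is not quantified.

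The third reply is that an observed 8-week trigger score would let the mixed model correct most of the shift. This stands if that score is retained.

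**Conclusion.** The conflict is explicit and must be reconciled. The session condition applies in one arm and depends on outcome and adherence after randomisation, so it does not fit an intention-to-treat analysis.

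The consequence is conditional. If the condition ends follow-up or drops data, a null result moves toward UBI by roughly 0.1 to 0.7 K10 points, about 2% to 17% of the 4-point target, under the assumed inputs listed above. The shift is largely removed if an observed 8-week score stays in the model, and absent if all follow-up data are collected and analysed. The direction is better supported than the size.

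Two stronger conclusions are tempting. One is that the plan as a whole biases the trial toward UBI; that would require the ambiguous sentence to override the other three statements. The other is a larger figure. Removing 10% of the UBI arm with a 12-point excess gives 0.10 × 12 / 0.90 = 1.33 points and a false-positive risk of about 16%. Both inputs to that figure are assumed, and it ignores the planned baseline adjustment.

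Severity: should be fixed.

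**What to change.** Reconcile the Participants and Intervention sections. For data collection and analysis:

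- Remove the condition on two of three sessions.
- State that every consented participant in both arms is followed at 8, 12 and 26 weeks and analysed as allocated, whatever the later K10, sessions attended or change of care.
- Separate stopping UBI or changing pathway from withdrawing consent to follow-up. Only the latter ends data collection.

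Decisions on a patient's care are left unchanged.

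The cost is protocol wording and a note to the research assistant, settled before unblinding. Questionnaires already go by mail or email on the same schedule in both arms, so no new visits or measures are needed.
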